##### Patient-related outcomes

Patient-related primary outcomes will test non-inferiority in change scores on key clinical outcome measures from pre- to post- intervention when comparing those patients treated under the old model care compared to those treated under the new model of care. Furthermore, % patients treated adequately at each step of the Stepped Care Model will be measured by the number of patients discharged from the service by the treating clinician with outcome measures indicating reliable clinical change from pre- to post- intervention. The Clinical outcome measures include the Insomnia Severity Index (ISI) [34], Depression Anxiety and Stress Scale (DASS-21) [35], Kessler Psychological Distress Scale (K10) [36], and the EuroQol (EQ-5D-5 L) [37].

**Insomnia Severity Index** (ISI) is a 7-item self-report questionnaire assessing the nature, severity, and impact of insomnia over the past two weeks on a 5-point scale from 0 = no problem; 4 = very severe problem. The measure is widely used in the literature as well as clinically where a score of 11 is indicative of likely meeting criteria for an insomnia disorder in clinical trials and a change score greater than 8 is the minimally important difference to be considered ‘markedly improved’ or in remission [34, 38].

**Depression Anxiety and Stress Scale** (DASS-21) is a short version of a 42-item self-report instrument designed to measure three related negative emotional states: depression, anxiety and tension/stress over the past 7 days. Items are scored on a 3-point scale from 0 (did not apply to me at all) to 3 (applied to me very much, or most of the time). Total scores represent symptoms of distress in each of the domains in the ‘normal’, ‘mild’, ‘moderate’, ‘severe’ and ‘extremely severe’ relative to population norms [35].

**Kessler Psychological Distress Scale** (K10): The K10 is a 10-item self-report scale to assess symptoms over the past 4 weeks. Items are rated on a 5-point scale from 1 (none of the time) to 5 (all of the time). A score of less than 20 represents low psychological distress ‘likely to be mentally well’. Between 20 and 24 represents moderate distress ‘may have a mild mental disorder’ and between 25 and 29 represents high psychological distress ‘likely to have a moderate mental disorder’ [36].

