*How effective was the model of care in achieving its intended outcomes?*	**Effectiveness** – impact on outcomes and quality of life/economic outcomes	**Primary outcomes** *Service Access Measures* • Average number of occasions of Service within Sleep Psychology service under ‘old’ model compared to ‘new’ model of care • Percentage of new patient activity under ‘old’ model compared to ‘new’ model of care • Average wait-time to access a first appointment with Sleep Psychology from date of referral under ‘old’ model compared to ‘new’ model of care • Average time to discharge from first appointment to final appointment with Sleep Psychology under ‘old’ model compared to ‘new’ model of care • Percentage of patients discharged from psychology *Patient-related Outcomes* • Change scores on clinical outcome measures pre- to post- treatment on clinical outcome measures (ISI, DASS-21, K10 and EQ-5D-5 L) comparing patients treated under ‘old’ model versus ‘new’ model of care • % patients treated adequately at each level of Stepped Care • Differences in patient characteristics (age, sex, geographical location, presenting issue) between those who are adequately treated at each level of the new model of care (moderation analysis) *Economic Outcomes* • Quality-adjusted life year calculations as a measure of cost-effectiveness of the ‘new’ model of care compared to the ‘old’ model of standard care **Secondary outcomes** *Patient satisfaction* • Patient satisfaction measure (SRS) post- treatment comparing patients treated under ‘old’ model versus ‘new’ model of care *Patient satisfaction with digital intervention* • Patient reported ease of access to digital intervention • Acceptability and relatability of the online program/service provided (rated by patients), including: i. motivation to access online treatment (diversion from public hospital services for insomnia treatment) ii. understanding of intervention materials iv. perceived change in sleep problem • Differences in patient characteristics (age, sex, geographical location, presenting issue) between those who complete the digital intervention compared to those who do not complete	Significantly fewer occasions of service under new model of care Significantly greater % new patient appointments under new model Significantly shorter wait-time to first appointment under new model Significantly shorter time to discharge under new model Outcomes are non-inferior under new model of care; upper bound 95%CI on outcome measures is less than MCID MCID is achieved on outcome measures by > 80% patients at each level The ‘new’ model is more cost effective Patient reported satisfaction is non-inferior under new model of care; upper bound 95%CI is less than MCID > 90% patients report positive experiences	Patient qualitative and quantitative surveys Medical Record Patient registration system

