*Was the model was delivered as intended?*	**Implementation -**consistency and fidelity of delivery as intended and the time and cost of the intervention	• % of model of care elements delivered as per protocol • Differences in % of model of care elements delivered as per protocol compared between participating intervention staff • Differences in patient-related outcomes (%MCID achieved) compared between participating intervention staff • Number of psychology-led discharges from Direct to Psychology pathway (diversion from medical pathway) • Number of occasions of service per psychology resource (staffing) available comparing the ‘old’ and ‘new’ model of care • Direct service costs versus revenue generated for new and review consultations of the ‘new’ model of care compared to the ‘old’ model of standard care	> 90% intervention components are delivered as per the protocol Implementation adaptations are reported at dissemination No significant difference in % model of care elements delivered between intervention staff No significant difference in MCID achieved between intervention staff The new model of care is cost effective, less resource intensive and more time efficient than the old model of care	Medical Record Patient registration system Document review
*How sustainable is this model of care*,* how well can the model of care continue to operate into the future?*	**Maintenance – long term effects of the program**,** model is business as usual**	• % components of model still operating 6 months post completion of the study • Description of which components of the model are still operating 6 months post completion of the study • Demand for the service – number of Direct to Psychology referrals and patient assignment to the different ‘levels’ of the model 6 months post completion of the study • Evidence of scale and spread of similar models across other services internal and external to the health provider	> 95% of the model is still operating 6 months post completion (July 2026) Number of Direct to Psychology referrals and patient assignment to treatment levels are sufficient to justify ongoing service provision	Document review

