### Statistical analysis

The project will employ a mixed methods approach. Qualitative surveys for patients, multidisciplinary staff, and referrers was undertaken pre-service change to ascertain the acceptability of the digital therapy, as well as familiarity, access, confidence, and relatability of this treatment option [25]. Post-implementation surveys will also be undertaken on these same metrics. Quantitative data will be collected pre- and post-service change to ascertain treatment effectiveness in terms of clinical outcome measures, as well as service measures of interest such as patient flow, occasions of service and program engagement. Based on similar studies [40], and allowing for some incomplete data, we expect to have data for approximately 110 participants from each pre- and post- time period, resulting in a sample of 220 participants overall who will be suitable for the Direct to Psychology pathway. To assess wait times, participants will be categorised into four groups based on the time-period (pre/post implementation) and whether they met eligibility criteria for the Direct to Psychology pathway. Differences in wait times between the groups will be assessed using a one-way Analysis of Variance (ANOVA) and linear regression modelling. In a one-way ANOVA study, a sample of 220 participants, divided by 4 groups, achieves 80% power with a significance level of 0.05 to detect a moderate-large effect size (Cohen’s f) of 0.25 [41]. The effects of other variables of interest and potential confounders (patient characteristics, diagnosis,) will be tested in multivariable models. For differences in patient outcome measures pre- and post- intervention when comparing pre- and post- service change, the mean between-group difference and 95% confidence interval (CI) will be calculated. As this aspect of the evaluation is a non-inferiority trial (that is, we expect clinical outcomes to not be reduced due to the service change), the criteria adopted to determine non-inferiority will be if the upper bound 95%CI on each clinical outcome measure was less than the minimal clinical important difference (MCID). Quantitative data measuring pre- and post- service change outcomes on key indices of patient service satisfaction, service characteristics (e.g., occasions of service); as well as referrer and staff service satisfaction, and engagement with digital therapies, will be evaluated via univariate statistical tests where indicated such as independent samples t-test (or nonparametric equivalent), and categorical comparisons will be evaluated using Pearson’s chi-square. The distribution of outcome measures will be assessed, and appropriate transformations will be applied for use in modelling. Differences between group means will be tested using generalised linear regression modelling. Health related quality of life will be measured pre- and post- implementation using the EQ-5D-5 L. Population norms for EQ-5D-5 L Australia will be used to value the data set [42].

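### Comparing staff only on the percentage of patients reaching the MCID discards scale data the trial already holds, weakens the comparison, and makes its no-difference target easier to meet

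*Protocol article*

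**What the plan says.** In Table 1 of the protocol article, the Implementation row lists "Differences in patient-related outcomes (%MCID achieved) compared between participating intervention staff" as an indicator. The matching target is "No significant difference in MCID achieved between intervention staff". The parenthesis fixes the scale: each patient either reached the MCID or did not.

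The Effectiveness row treats the same instruments differently. For old versus new model it lists "Change scores on clinical outcome measures pre- to post- treatment on clinical outcome measures", naming the ISI, DASS-21, K10 and EQ-5D-5L. The Statistical analysis section reports that comparison as a mean between-group difference with a 95% CI. The same section provides for regression modelling of group means, and says that "categorical comparisons will be evaluated using Pearson’s chi-square".

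The article gives no reason for using the cut score in the staff comparison. It states no number of staff, caseload per staff member, SD or power for it.

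**The concern.** Once a change score is reduced to reached or not reached, distance from the threshold no longer counts. For the ISI the article says "a change score greater than 8 is the minimally important difference to be considered ‘markedly improved’ or in remission". On that rule a patient who improves by 8 points counts the same as one who gets worse, and one who improves by 9 counts the same as one who improves by 20. A staff member whose patients improve less on average shows up only through those who cross the line.

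Two features make this matter more here than in an ordinary secondary comparison. The new model passes part of the treatment to supervised interns, and this is the row that compares outcomes between the people who deliver it. And the target is met by failing to find a difference, so every loss of power raises the chance that a real shortfall passes as success.

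**Working it through.** **The plan's own figure.** There is none for this comparison. The only power statement concerns wait times: a one-way ANOVA with N = 220, four groups and f = 0.25, stated as 80%. With noncentrality 220 × 0.25² = 13.75 and 3 and 216 degrees of freedom, power is 88.4%. That statement is conservative and has no bearing on the staff comparison.

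**Inputs from the article.**
- Sample: "we expect to have data for approximately 110 participants from each pre- and post- time period". This is used only to set the scale of the larger caseloads below.
- A reference MCID rate of 80%, borrowed from the per-level target "MCID is achieved on outcome measures by > 80% patients at each level". It is varied from 50% to 90%.

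**Assumptions not in the article.** Two staff or grades with equal caseloads n; normal change scores with a common SD; a true difference d = 0.5 SD (for example 3 ISI points with an SD of 6); two-sided 5%.

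**Formulas.**
- Full scale: two-sample t-test, noncentrality d × √(n/2), 2n − 2 degrees of freedom.
- Cut scale: if the better group reaches the MCID at rate p1, the other reaches it at p2 = Φ(Φ⁻¹(p1) − d). Power is that of the uncorrected chi-square on p1 versus p2, summed over all binomial outcomes.

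**Worked case, n = 55, p1 = 80%.**
- p2 = Φ(0.842 − 0.5) = Φ(0.342) = 63%.
- Full scale: noncentrality 0.5 × √27.5 = 2.62, power 73.8%. Hand check by normal approximation: Φ(2.62 − 1.96) = 75%.
- Cut scale: exact power 49.4%. Hand check: pooled rate 0.717, null SE √(2 × 0.717 × 0.283 / 55) = 0.0859, alternative SE √((0.8 × 0.2 + 0.634 × 0.366) / 55) = 0.0844, so Φ((0.166 − 1.96 × 0.0859) / 0.0844) = 49%.
- Loss: 73.8 − 49.4 = 24 points.

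**Across caseloads** (power in %, d = 0.5 SD):

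| n per group | Full scale | Cut, p1 = 50% | 60% | 70% | 80% | 90% | Loss, points |
|---|---|---|---|---|---|---|---|
| 10 | 18.5 | 12.0 | 12.6 | 11.9 | 10.1 | 5.9 | 6 to 13 |
| 20 | 33.8 | 22.6 | 21.7 | 22.8 | 22.1 | 16.9 | 11 to 17 |
| 27 | 43.8 | 28.7 | 28.1 | 28.8 | 28.8 | 23.2 | 15 to 21 |
| 37 | 56.4 | 38.0 | 39.2 | 37.8 | 35.9 | 28.6 | 17 to 28 |
| 55 | 73.8 | 53.6 | 53.2 | 53.7 | 49.4 | 39.4 | 20 to 34 |

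Simulation of the t-test against chi-square agrees: 74% v 50% at 55 each and 56% v 36% at 37 each, with p1 = 80%.

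**More than two staff.** With whole-number ISI changes, SD 6, one staff member 3 points worse and p1 = 80%, simulated power is 59% v 38% for three staff with 37 patients each, and 43% v 27% for four with 27 each.

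**Other differences.** Over 210 scenarios (differences of 0.3 to 0.8 SD, rates of 50% to 90%, 15 to 55 patients each or unequal splits), by normal approximation, the loss ran from about 3 to 36 points with a median of about 18. The cut lowered power in every one.

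**The case against.** **The choice is coherent.** The row belongs to the Implementation domain, is not labelled a primary or secondary outcome, and uses the same yardstick as the per-level target. The main clinical comparison stays on the full scale. This stands as a reason to rate the point low. It does not justify dropping the scale scores, because the MCID percentage can be kept beside them at no cost.

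**Intern care is checked elsewhere.** A reader might infer that this row is the only planned check on delegated care. The documents do not support that. The Patient-related outcomes section and the Effectiveness row also report the share adequately treated at each level, and one level is one-to-one treatment by an intern. That outcome sets a target per level, however; it does not test between staff, and it relies on the same kind of cut.

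**No single figure is fixed by the document.** A reader might take one power loss from the table as a fact about this trial. It is not one. The 110 are patients suitable for the Direct to Psychology pathway, not a therapist caseload. Others reach psychology through Standard Care, the digital level has no treating therapist, and groups are run by a psychologist and an intern together. Caseloads of 55 or 37 are illustrations, and with few patients each the loss is smaller. This stands; only the direction of the effect is certain.

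**The chi-square test is inferred.** The sentence naming it covers satisfaction, service characteristics and engagement, and does not mention the staff comparison. This stands too, but the loss comes from the cut: another test on the binary outcome would not recover the discarded information.

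**A better scale does not cure the target.** A reader might infer that full-scale analysis would make a non-significant result evidence that staff perform alike. It would not: at 20 to 37 patients each, full-scale power for 0.5 SD is only 34% to 56%.

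**Conclusion.** The point holds in a limited form. Table 1 fixes a binary outcome for the staff comparison while the same scores are kept on the full scale for another comparison, and under a target met by non-significance the weaker test favours the desired answer. Under the stated assumptions at 0.5 SD, the loss grows from about 6 to 13 points at 10 patients each to about 20 to 34 at 55. The size depends on an SD, a staff difference and caseloads that the article does not give. The comparison is an implementation indicator, so no primary conclusion depends on it. This is an inexpensive improvement and does not threaten the evaluation.

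**What to change.** Change the Table 1 indicator to the difference between staff in post-treatment score on the ISI, DASS-21, K10 and EQ-5D-5L, from a linear model adjusted for the baseline score and reported with its 95% CI. Keep the percentage reaching the MCID for each staff member as a descriptive figure. Reword the target so that the CI is read for the largest shortfall it still allows, and non-significance is not taken as evidence that staff results are the same.

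The cost is one line of Table 1, its target and a sentence in the Statistical analysis section. No new data are needed. The result comes in scale points, which are less immediate than a percentage; the retained descriptive figure covers that.

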### Level 4: 1:1 with experienced Psychologist

Patients assigned to this level will undergo treatment 1:1 with the experienced Psychologist. The experienced Psychologist will monitor participation and clinical outcomes during the 1:1 intervention program, and provide additional evidence -based strategies depending on sleep or mental health comorbidities (as described in Level 3 above). Discharge or on-referral will be provided at the conclusion of the treatment.

For Levels 2 to 4 - sessions will be delivered flexibly either face-to-face or via telehealth.

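### Table 1 counts a non-significant test as proof of consistency between staff, a rule that gets easier to meet as patient numbers fall

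*Protocol article*

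**What the plan says.** Table 1 of the protocol article (Implementation and evaluation – RE-AIM) describes the Implementation domain as "consistency and fidelity of delivery as intended and the time and cost of the intervention". One indicator in that row is "Differences in patient-related outcomes (%MCID achieved) compared between participating intervention staff". The target column gives the success criteria as "No significant difference in MCID achieved between intervention staff" and, for fidelity, "No significant difference in % model of care elements delivered between intervention staff". Neither has a margin or a confidence-interval rule. The article does not state the number of staff, the patients per clinician or the power for these comparisons.

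On sample size, the Statistical analysis section says "we expect to have data for approximately 110 participants from each pre- and post- time period". Its only power statement concerns wait times: the ANOVA "achieves 80% power with a significance level of 0.05 to detect a moderate-large effect size (Cohen’s f) of 0.25". For tests on proportions it says "categorical comparisons will be evaluated using Pearson’s chi-square".

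On who treats whom, Level 3 is delivered by psychology interns under supervision. For Level 4, "Patients assigned to this level will undergo treatment 1:1 with the experienced Psychologist". Patients are matched to a level on clinical grounds, not randomised.

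**The concern.** The domain is meant to show that delivery and results are alike across staff. A significance test with no margin cannot show that. It can find a difference or fail to find one, and failure becomes more likely as the groups shrink. A thin or incomplete dataset would therefore help the service meet its target.

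The article handles its other claim of this kind differently. For old-model versus new-model outcomes it requires a 95% confidence bound to lie inside the MCID. The staff comparison has no equivalent.

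There is also a case-mix problem. Interns treat at Level 3 and the experienced Psychologist at Level 4, so a comparison across those levels reflects both who delivered care and which patients were sent there. The target could be missed with no staff problem, or met despite one. The Background gives delegation to junior staff as one response to service pressure, so a misleading statement of consistency would matter to readers of the evaluation.

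**Working it through.** **The plan's own power figure.** It is for wait times: 4 groups, N = 220, f = 0.25, alpha 0.05. The noncentrality is 220 × 0.25² = 13.75. With F on 3 and 216 degrees of freedom, power is 88.4%, against 80% stated. The stated figure is conservative and says nothing about the staff comparison.

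**Inputs for the staff comparison.**
- 110 new-model patients (Statistical analysis section).
- Reference MCID rate of 80%, taken from the Table 1 target of more than 80% at each level.
- Pearson chi-square, two-sided alpha 0.05.
- Assumed, because the article is silent: two to six staff, an equal split, and one clinician worse than the rest.

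**Two staff, 55 patients each, 80% v 60%, by formula.**
- Standard error under no difference: √(2 × 0.7 × 0.3 / 55) = 0.0874.
- Standard error under the difference: √((0.16 + 0.24) / 55) = 0.0853.
- Power = Φ((0.20 − 1.96 × 0.0874) / 0.0853) = Φ(0.34) = 63%, so the difference is missed 37% of the time. Exact binomial calculation gives 36%.

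**Chance of a non-significant result** (simulated k × 2 chi-square, good to about one point; two-staff column agrees with exact calculation):

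| Deficit of one clinician | 2 staff | 3 | 4 | 5 | 6 |
|---|---|---|---|---|---|
| 10 points | 77% | 83% | 88% | 90% | 91% |
| 20 points | 36% | 51% | 63% | 70% | 76% |
| 30 points | 7% | 18% | 31% | 41% | 52% |

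**Sensitivity to the number of patients.** With only 60 attributable patients, a 20-point deficit is missed 61% of the time with two staff, rising to 86% with six.

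**Patients needed.** For 80% power at 80% v 60%: (1.96 × √0.42 + 0.84 × √0.40)² / 0.20² ≈ 81.2, so 82 per clinician. For 80% v 70% it is 294. An equal split of 110 gives 55 each with two staff and about 27 each with four.

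**Precision.** With both clinicians at 80%, the 95% interval half-width is 1.96 × √(2 × 0.16 / n): about 15 points at n = 55 and 21 points at n = 27.

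**Case mix.** Suppose Level 3 and Level 4 patients truly differ (80% v 60%) and clinicians have no effect. A comparison that ignores level is significant 37% of the time at 28 per group and 63% at 55 per group.

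No power was computed for the delivered-elements target, because the article gives neither its unit of analysis nor a usable rate beyond the overall target of more than 90%.

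**The case against.** **Will the test usually miss a clearly worse clinician?** A reader might infer this, but the documents do not support it. Staff numbers are unstated, and with two equally loaded staff a 20-point deficit is detected more often than not. A 30-point deficit is missed in under half of cases with five or fewer staff. The denominator is uncertain too. Standard-pathway patients also enter Stepped Care, which could raise it above 110. Level 1 is self-guided, so some patients may belong to no clinician, which would lower it.

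**Is the comparison unadjusted?** A reader might infer this as well. The article does not say so. It plans multivariable models for potential confounders, naming patient characteristics and diagnosis but not treatment level, and a separate analysis plan could add level. The chi-square sentence does not expressly cover the staff comparison either. What stands is structural: where staff type and level coincide, adjustment for level removes the contrast and does not correct it.

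**Do other targets cover this?** In part. Table 1 also requires the MCID to be reached by more than 80% of patients at each level, and more than 90% of components to be delivered as planned. A poor overall result among interns at Level 3 would fail the first target whatever the staff test showed. Neither target would expose one weak clinician within a level.

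**Does the plan rest scale-up on equality between interns and the senior psychologist?** No. The Discussion ties future use and scalability to acceptability, and these are two cells in one implementation row.

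None of this rescues the criterion. It is a stated rule that counts failure to reject as success, not a detail left to another document.

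**Conclusion.** The point holds as a fault in the decision rule. Followed as written, both targets declare consistency whenever a test is non-significant, and they reward small numbers.

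The size for MCID rates depends on the assumed staff count. With 110 patients split equally and the other staff at 80%, a clinician at 60% is missed about 36% (two staff), 51% (three) or 63% (four) of the time. A 10-point deficit is missed 77% to 91% of the time with two to six staff. For delivered elements the logic is the same, but no figure can be given.

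Separately, comparisons across Levels 3 and 4 cannot separate staff from case mix. The matter concerns implementation targets and leaves the primary outcomes untouched. It should be corrected because the change is small.

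**What to change.** Replace both targets that rest on the absence of a significant difference. For delivered elements and for MCID achieved, report each staff member's (or staff group's) estimate and the between-staff difference with its 95% confidence interval. Make the comparison within a treatment level where more than one clinician delivers that level, and label it descriptive. State that a non-significant result or a wide interval will be reported as inconclusive, not as consistency.

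A pass/fail margin is not advised at these numbers. With two identical clinicians at 80%, an interval lying wholly within ±15 points would occur only about 8% of the time at 55 patients each, and under 1% at 27 each.

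The cost is two table cells and one sentence in the Statistical analysis section. The drawback is that the row no longer gives a yes/no answer, and the likely result is inconclusive.
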